**Table 3 T3:**
[figure not shown]
Primary and secondary endpoints.

The primary endpoint is defined as an improvement of hemodynamics with a decrease in the vasopressor dependency index (VDI) of at least 20% within 48 h compared to the baseline measurement immediately before the onset of therapy with CytoSorbents (CytoSorb). For patients without vasopressor therapy at baseline, the primary endpoint is defined as an improvement in CPI of at least 20%.

The VDI is defined as the ratio of the inotropic score divided by mean arterial pressure (MAP):

VDI = inotropic score / MAP

The inotropic score is defined as (dopamine dose_1) + (dobutamine dose∗1) + (adrenaline dose∗100) + (noradrenaline dose∗100) + (phenylephrine dose∗100). All doses are given as μg/kg/min.

TPTD will be performed at baseline as well as after 6, 8, 12, 16, 24, 30, 32, 36, and 48 h after the initiation of blood purification.

Outcome analysis will be based on a comparison of the incidence of the primary endpoint in 30 intervention patients compared to 60 matched controls with advanced hemodynamic monitoring recruited from recent studies in SAP within the same setting and the same centers. To account for different numbers of TPTD measurements in the controls (usually 2–3 measurements within 24 h), the primary outcome analysis will be performed based on the measurements at baseline as well as after 12, 24, 36, and 48 h after the initiation of CytoSorb-therapy.

APACHE-II-score on inclusion and baseline VDI are the main criteria for matching.

Secondary analyses will include laboratory (cytokine levels) and translational endpoints (including multiplex-ELISAs of numerous anti- and pro-inflammatory cytokines/chemokines and DNA analyses).

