### Statistics

1.3

The incidences of the primary endpoint and all dichotomous secondary endpoints will be compared using the Chi-Square test or Fisher exact test as appropriate.

All comparisons of continuous endpoints within groups and between groups will be performed using *t* test or Wilcoxon-test for paired or unpaired samples as appropriate.

A p-value of *P*<.05 is considered as significant.

Missing values over time will be replaced using “last value carried forward”.

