#### Power calculation

1.3.1

Power calculation is based on the assumption that the primary endpoint is fulfilled in 67% of the 30 patients in the intervention-group and in 33% of the 60 matched controls. This results in a statistical power of 87.8% (https://www.dssresearch.com/KnowledgeCenter/toolkitcalculators/statisticalpowercalculators.aspx).

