With regard to the complexity of numerous diagnostic and therapeutic approaches in SAP, the impact of single measures such as 2-day extracorporeal cytokine elimination should not be overestimated. Necessarily, this has to be considered for the study design, in particular for the primary endpoint and the power calculation. Therefore, we chose changes in the VDI as the primary endpoint. VDI has been repeatedly used as an endpoint in studies focused on extracorporeal cytokine and toxin elimination.^[12,18]^

Patients similar to the patients selected according to the inclusion criteria of PACIFIC have been treated by most PACIFIC study centers during the randomized controlled EAGLE-trial (https://clinicaltrials.gov/ct2/show/NCT00894907). The EAGLE-study investigates the impact of TPTD guided volume resuscitation on outcome. Half of the intended number of 182 patients of the EAGLE-study will be under hemodynamic monitoring with the PiCCO-device. Since the inclusion criteria and the clinical setting are nearly identical as for PACIFIC, data from patients from the EAGLE-study with PiCCO-monitoring will be a major source for the allocation of matched controls.

In addition to the primary endpoint and several standard secondary outcomes such as organ failures and mortality, the PACIFIC-trial will analyze several measures of inflammation at baseline and over time. The importance of pro-inflammatory cytokines in pancreatitis has been highlighted by a recent study in 84 patients with AP who were screened for known polymorphisms in TNFα, interleukin 1 (IL-1), IL-1 receptor antagonist (IL1RN), IL-6, and IL-10. The study demonstrated that the TNFα −238 AG genotype, but not the TNFα −308 SNP, was associated with organ failure (shock and/or respiratory failure) during AP.^[19,20]^ A very interesting candidate that seems to drive the pathophysiology of MOF during AP in experimental animal models is IL-6. IL-6 not only regulates the acute phase response in the liver, it can also activate a plethora of pro-inflammatory pathways, such as Stat3 and NF-kappaB.^[21]^

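### Carrying the last value forward, then testing it as if measured, biases the continuous secondary endpoints when the groups have unequal gaps; the case is firmest for hemodynamics, and the size rests on assumptions

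*Protocol article*

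**What the plan says.** Section 1.3 (Statistics) of the protocol article gives one rule for incomplete follow-up: "Missing values over time will be replaced using" last value carried forward. It names no exception, alternative or sensitivity analysis. The same section says "All comparisons of continuous endpoints within groups and between groups will be performed using" a t test or Wilcoxon test, and "A p-value of *P*<.05 is considered as significant".

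Section 1.2.3 (Outcomes) sets the hemodynamic schedule for treated patients: "TPTD will be performed at baseline as well as after 6, 8, 12, 16, 24, 30, 32, 36, and 48 h" after the start of blood purification. That is nine times after baseline. Controls usually have two or three measurements within 24 h. "To account for different numbers of TPTD measurements in the controls", the article reduces the grid to baseline, 12, 24, 36 and 48 h, but says so for the primary outcome analysis only.

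The Discussion adds that "the PACIFIC-trial will analyze several measures of inflammation at baseline and over time". It describes cytokine and chemokine levels as measured before and after use of the adsorber. It also says that many controls will come from another trial, EAGLE.

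**The concern.** Carry-forward assumes that a measure stays where it was last seen. Section 1.2.1 describes the inclusion window as the early phase of the disease, including its first inflammatory peak, and the aim of the trial is to change hemodynamics. A carried value is therefore too early: too high for a falling measure, too low for a rising one.

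If both groups have the same share of filled values and the same course, the error cancels in the group difference. If controls have more, they seem to improve less than they did, and CytoSorb gains an apparent effect. The controls' sparser measurement makes unequal filling plausible for hemodynamics. A t or Wilcoxon test cannot tell a filled value from a measured one, so the P-value carries the error too. At stake are the estimates and P-values of the secondary continuous endpoints. The yes/no primary endpoint is not examined here.

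**Working it through.** **The plan's own figure.** Section 1.3.1 assumes that "the primary endpoint is fulfilled in 67% of the 30 patients in the intervention-group and in 33% of the 60 matched controls", and adds "This results in a statistical power of 87.8"%. Pooled rate = (30 × 0.67 + 60 × 0.33)/90 = 0.4433. Null SE = √(0.4433 × 0.5567 × (1/30 + 1/60)) = 0.1111. Alternative SE = √(0.67 × 0.33 × (1/30 + 1/60)) = 0.1051. Then z = (0.34 − 1.96 × 0.1111)/0.1051 = 1.16, giving a two-sided power of 87.8%. The figure reproduces, and this point does not affect it.

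**Inputs.** From the article: 30 versus 60 patients, the carry-forward rule, t tests at 5%, and the two measurement frequencies. Assumed, because the article gives no values: no true effect; marker SD 1; correlation 0.7 over 24 h; natural decline of 0.3, 0.5 or 0.8 SD per day in both groups; missing at 48 h in 9% of treated patients and 30% or 39% of controls.

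**Bias.** If a measure falls by Δ over the gap, each filled value is Δ too high. The bias in (CytoSorb − control) is (m_T − m_C) × Δ, where m is the missing fraction.

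- 12 h carry, 9% versus 30%: Δ = 0.15/0.25/0.40 SD, so bias = −0.21 × Δ = −0.03/−0.05/−0.08 SD.
- 24 h carry, 9% versus 30%: Δ = 0.3/0.5/0.8 SD, so bias = −0.06/−0.11/−0.17 SD.
- 24 h carry, 9% versus 39%: bias = −0.30 × Δ = −0.09/−0.15/−0.24 SD.

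**Type I error by simulation** (nominal 5%; declines of 0.3/0.5/0.8 SD per day; 20,000 runs for the 12 h and 24 h rows, 4,000 for the dropout rows):

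| Gap pattern | 9% vs 30% missing | 9% vs 39% missing |
|---|---|---|
| Random gaps, carried 12 h | 5.2/5.6/6.5% | 5.2/6.5/7.8% (repeat runs: up to about 9%) |
| Random gaps, carried 24 h | 5.9/7.1/10.6% | up to about 17% |
| Permanent dropout, completely random | 6.9/10.2/15.8% | up to about 30% |
| Permanent dropout, likelier after a high value | 8.6/11.1/16.9% | 12/20/31% |

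In the last row, 9% versus 30% gives false differences of 0.14/0.20/0.30 SD in favour of CytoSorb.

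**Second design, as a check.** Five visits (0/12/24/36/48 h), correlation 0.6 between adjacent visits, random permanent dropout with the last visit uniform over 0-36 h, and a fall of 1 SD over 48 h. The mean time missed is (48 + 36 + 24 + 12)/4 = 30 h, so Δ = 30/48 = 0.625 SD. At 5% versus 30% missing the formula gives −0.25 × 0.625 = −0.156 SD; simulation gives −0.156 SD and type I error 9.9%. With the imbalance reversed (30% versus 5%), the bias is +0.156 SD and type I error 10.6%.

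**Equal missingness.** At 20% in both groups and no effect, type I error is 5.0%. A true effect building linearly to 0.60 SD shrinks to 0.60 × (1 − 0.20 × 0.625) = 0.525 SD; simulation gives 0.525.

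**Before/after comparison of cytokines.** If a fraction m of the after-values is filled with the before-value, the mean change is multiplied by (1 − m). With m = 20% as an illustration, 80% of the true change remains.

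**The case against.** Three objections carry weight.

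**Size.** A reader might infer a false-positive rate of 17-31%. The article does not support that. Two or three readings within 24 h means one about every 8-12 h, which is compatible with values near 24 h and 48 h. It suggests short intermittent gaps, for which type I error stays at about 5-9%. The high figures need lasting dropout that is much commoner in controls, and nothing in the article shows this.

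**Markers.** A reader might also infer that controls would falsely appear to stay inflamed longer. The article describes cytokines before and after CytoSorb and nowhere says that controls have serial cytokine values. The endpoint and schedule tables are not reproduced in the text at hand, so that between-group contrast cannot be assumed.

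**Remedy.** A mixed model assumes that missingness depends only on observed values, and it implicitly extrapolates past death. The article quotes a mortality of about 42% in severe disease, so the model alone is not a clean answer. This stands, and the change needs a rule for deaths.

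That a separate analysis plan may say more does not answer the point: the rule is stated, without restriction, in the protocol itself.

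**Conclusion.** The point holds in limited form. The stated rule biases between-group comparisons of changing continuous secondary endpoints whenever the filled fractions differ. It is firmest for hemodynamics; for cytokines only the understated before/after change is supported.

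Under the assumptions above, type I error is about 5-9% for 12 h gaps, 6-17% for 24 h gaps and 7-31% for permanent dropout. The article does not say which pattern applies, though its description of the controls fits the short gaps best. The direction is not fixed: more gaps in controls favour CytoSorb for an improving measure, and more gaps in treated patients work against it. Equal missingness brings no false-positive inflation, only dilution of an effect that builds over time. The change is worth making because the rule is explicit, a better one is available and the cost is low.

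**What to change.** For continuous endpoints measured over time, make the main analysis a likelihood-based mixed model for repeated measures. Fit it to recorded values only (log scale for cytokines), with group, time, group-by-time and baseline value, and report the group difference at the stated time points. For cytokines available only in treated patients, use the same approach without the group terms.

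Do not carry values past death. Report deaths before each time point by group and state that the estimate refers to patients alive, or add a sensitivity analysis that ranks death as the worst outcome. Keep last value carried forward at most as a sensitivity analysis.

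The cost is a few sentences in section 1.3 and slightly more analysis work. The price is a missing-at-random assumption and the need for a suitable scale. No new data are required.

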#### Power calculation

1.3.1

Power calculation is based on the assumption that the primary endpoint is fulfilled in 67% of the 30 patients in the intervention-group and in 33% of the 60 matched controls. This results in a statistical power of 87.8% (https://www.dssresearch.com/KnowledgeCenter/toolkitcalculators/statisticalpowercalculators.aspx).

### Data management

1.4

Data including baseline data and medical history as well as side effects will be documented in a pre-defined case report form. Data will be transferred to a central database at the center of the principal investigator.

Patients will be followed up until discharge or death.

## Discussion

2

AP is a common diagnosis worldwide. More than 240,000 cases per year are reported in the United States alone. The outcome of AP largely depends on the severity of the disease. Still, it remains a challenge to accurately assess the severity of AP during its early stages. Although recent studies have deepened our understanding of the pathophysiology, most current therapies remain directed at relief of symptoms rather than improving outcome, apart from sphincterotomy for gallstone pancreatitis. While surgery for AP is mainly reserved for severe complications, other therapies such as fluid resuscitation,^[6,14]^ antimicrobial therapy,^[15]^ drainage procedures,^[16]^ and endoscopic management of complications define the current standard of care.

Due to the lack of *causative* therapeutic approaches, the concept to limit local and systemic inflammation is appealing. Acinar cell damage leads to a local inflammatory response but inflammatory mediators also enter the general circulation. These mediators play a key role in AP and the resultant multiple organ dysfunction or MOF syndrome, which is the primary cause of death in patients with SAP. The severity of an attack of AP appears to be determined by the magnitude of the resultant systemic inflammatory response. While excessive stimulation of the immune system accounts for the early systemic complication, immune paralysis, also termed compensatory anti-inflammatory response syndrome, contributes to the local and septic problems in the late phase.

However, several pharmacological approaches including anti-oxidative strategies with vitamin C, selenium and n-acetylcysteine^[8]^ as well as platelet factor antagonists^[9]^ have not resulted in improved outcome for patients with SAP. Compared to these more specific pharmacological approaches, the extracorporeal removal of large amounts of cytokines might be a more immediate and effective approach, in particular in the *early* phase of SAP.

Therefore, this study restricts inclusion to a maximum of 7 days after the onset of pain. Also considering the resources required and the imminent risks of an extracorporeal circuit with anticoagulation, only patients with SAP and a high risk of organ failure will be included. The main criterion for severity is an APACHE-II-score ≥10. Baseline values and changes of APACHE-II are strongly associated with severity and outcome of AP.^[17]^

With regard to the complexity of numerous diagnostic and therapeutic approaches in SAP, the impact of single measures such as 2-day extracorporeal cytokine elimination should not be overestimated. Necessarily, this has to be considered for the study design, in particular for the primary endpoint and the power calculation. Therefore, we chose changes in the VDI as the primary endpoint. VDI has been repeatedly used as an endpoint in studies focused on extracorporeal cytokine and toxin elimination.^[12,18]^

Patients similar to the patients selected according to the inclusion criteria of PACIFIC have been treated by most PACIFIC study centers during the randomized controlled EAGLE-trial (https://clinicaltrials.gov/ct2/show/NCT00894907). The EAGLE-study investigates the impact of TPTD guided volume resuscitation on outcome. Half of the intended number of 182 patients of the EAGLE-study will be under hemodynamic monitoring with the PiCCO-device. Since the inclusion criteria and the clinical setting are nearly identical as for PACIFIC, data from patients from the EAGLE-study with PiCCO-monitoring will be a major source for the allocation of matched controls.

In addition to the primary endpoint and several standard secondary outcomes such as organ failures and mortality, the PACIFIC-trial will analyze several measures of inflammation at baseline and over time. The importance of pro-inflammatory cytokines in pancreatitis has been highlighted by a recent study in 84 patients with AP who were screened for known polymorphisms in TNFα, interleukin 1 (IL-1), IL-1 receptor antagonist (IL1RN), IL-6, and IL-10. The study demonstrated that the TNFα −238 AG genotype, but not the TNFα −308 SNP, was associated with organ failure (shock and/or respiratory failure) during AP.^[19,20]^ A very interesting candidate that seems to drive the pathophysiology of MOF during AP in experimental animal models is IL-6. IL-6 not only regulates the acute phase response in the liver, it can also activate a plethora of pro-inflammatory pathways, such as Stat3 and NF-kappaB.^[21]^

Given the importance of cytokines in AP and the mode of action of CytoSorb, the PACIFIC-study will analyze cytokine and chemokine levels before and after the usage of CytoSorb adsorber. Such analysis will include multiplex-ELISAs of numerous anti- and pro-inflammatory cytokines/chemokines. In an explorative part of the study, DNA from the blood of these patients will be extracted for genetic analysis, particularly with respect to SNPs of factors of interest. All these analyses will add significant information to the PACIFIC studies.

### Trial status

2.1

The study will start recruitment in October 2018. A number of pilot data have been collected between January 2016 and July 2018. These data will be published separately from the PACIFIC study.
